## Methods

### Study Design

This is a phase IV, prospective, multicenter, observational, cohort study designed to evaluate the effectiveness of AlloSure dd-cfDNA (CareDx Inc, Brisbane, CA) surveillance and patient care management in kidney transplant patients in prolonging allograft survival, allograft function, and immunological status. All prospective data will be collected from patient electronic medical records. Propensity-matched control data will be sourced from United Network for Organ Sharing U.S. Scientific Registry of Transplant Recipients databases. The study duration will be event driven, with each patient’s enrollment lasting 5 years.

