**Methods:**

The study protocol will acquire data from a phase IV observational trial to assess a cohort of renal transplant patients managed using AlloSure dd-cfDNA and patient care managers versus 1000 propensity-matched historic controls using United Network for Organ Sharing U.S. Scientific Registry of Transplant Recipients data. Data will be managed in a centralized electronic data server. The primary outcome will be superior allograft survival, as a composite of return to dialysis, retransplant, death due to allograft failure, and death with a functional graft (infection, malignancy, and cardiovascular death). The secondary endpoints will assess improved kidney function through decline in estimated glomerular filtration rate and immune activity through development of donor-specific antibodies.

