### Outcomes and Measures

The primary endpoint of this study will be superior graft survival measured as the time to allograft loss, defined as the composite of return to dialysis, retransplant, death due to allograft failure, and DWFG (infection, malignancy, and cardiovascular death).

Secondary endpoints include assessment of allograft function and immunological status. Allograft function will be measured as the relative change in eGFR from baseline between the 2 study groups: dd-cfDNA surveillance compared to controls. Immunological status will be defined by detection of de novo DSA formation in patients monitored using dd-cfDNA compared to the matched controls.

All clinical events and investigation results will be captured through the patient electronic medical record or via AlloCare, an optional smartphone-based application that provides a patient-driven platform to manage medications, access results, monitor wellness activities, and streamline communication with their care team. Patients will also be offered mobile phlebotomy when they are unable to visit a local laboratory. The mobile blood draw will be coordinated by CareDx, which will draw all regular tests, urine samples, as well as the AlloSure. Support for testing adherence will be provided by PCMs (CareDx Inc, Brisbane, CA) to assist with scheduling both in-center and mobile draws and provide laboratory visit reminders.

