### Testing Schedule

Patients will have quarterly AlloSure dd-cfDNA testing (every 3 months) as part of their posttransplant surveillance for a period of 5 years. DSA, eGFR, routine transplant bloods, and clinical events will be captured using the standard of care regime as per institutional guidelines (Figure 1).

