**Exclusion Criteria**
Participant who is pregnant, lactating, or planning pregnancy during the trialSignificant hepatic impairment (determined by the principal investigator)Participant with life expectancy of <6 months or inappropriate for diagnostic monitoring through regular blood sampling<6 months and >18 months posttransplantAny other significant disease or disorder which, in the opinion of the investigator, may either put the participants at risk because of participation in the trial or may influence the result of the trial or the participant’s ability to participate in the trialParticipants who have participated in another research trial involving an investigational product in the past 12 weeksRecipients of multiorgan transplant (eg, kidney-pancreas)Recipients of a transplant from a monozygotic (identical) twinRecipients of nonautologous bone marrow transplantPatients with a history of poor compliance or needle phobia

A 2-sided log-rank test with an overall sample size of 3500 kidney transplant patients (of which 2500 will be periodically assessed with AlloSure and 1000 are matched controls receiving standard of care) achieves 87% power at a 5% significance level to detect an allograft survival difference of 5% (ie, 75%, AlloSure assessed; 70%, standard of care) during the 5-year surveillance period. This corresponds to a hazard ratio of 0.807, which is a 19.3% reduction in the risk of allograft loss in the AlloSure-assessed patients in comparison to standard of care. There is no consideration of patients lost to follow-up due to the United Network for Organ Sharing U.S. Scientific Registry of Transplant Recipients database, which tracks transplanted organ survival for all organ transplant recipients; however, this analysis does account for an attrition rate of 65%.

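### The protocol names different sources for primary events in the two groups (medical record or app versus national registry), and its loss-to-follow-up argument does not settle which source applies to AlloSure patients

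*Protocol article*

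**What the plan says.** Three places in the protocol article bear on where primary events come from.

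- **Study Design.** For enrolled patients: "All prospective data will be collected from patient electronic medical records". The next sentence deals with the comparison group: "Propensity-matched control data will be sourced from United Network for Organ Sharing U.S. Scientific Registry of Transplant Recipients databases". The abstract describes the comparison as AlloSure patients "versus 1000 propensity-matched historic controls using United Network for Organ Sharing U.S. Scientific Registry of Transplant Recipients data".
- **Outcomes and Measures, Testing Schedule.** The primary endpoint is time to allograft loss, a composite of return to dialysis, retransplant and death, with deaths classified by cause. On capture: "All clinical events and investigation results will be captured through the patient electronic medical record or via AlloCare, an optional smartphone-based application". Testing Schedule adds that "clinical events will be captured using the standard of care regime as per institutional guidelines".
- **Sample-size paragraph (printed after the exclusion criteria).** Loss to follow-up is not considered because of the registry, "which tracks transplanted organ survival for all organ transplant recipients". The same sentence says that the calculation allows for 65% attrition.

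The article does not name the registry as an event source for AlloSure patients, and it describes neither a linkage nor a common ascertainment rule for the primary endpoint.

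**The concern.** A log-rank comparison assumes that a graft loss has the same chance of being recorded, at the same time, in both groups. Here the named sources differ by group. Dialysis, retransplant and death can all happen away from the community practice that holds the record, and a patient-driven app cannot be relied on to report its user's death. About 20 community practices take part under shared care with transplant centers, so events outside the enrolling practice are to be expected.

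The effect sought is 5 percentage points over 5 years, so a modest difference in capture could produce or hide it. Propensity matching balances baseline characteristics and does nothing for outcome ascertainment. A larger sample would only make a spurious difference more significant.

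The direction is not fixed. Losses missed outside the practice would favour AlloSure. Closer surveillance of AlloSure patients, or under-reporting in the registry, would work against it.

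**Working it through.** **Inputs from the sample-size paragraph.** 2500 AlloSure patients and 1000 controls; 5-year graft survival 75% versus 70%; two-sided 5% log-rank test; hazard ratio 0.807; power 87%.

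**Reproducing the plan's figure.**
- HR = ln(0.75)/ln(0.70) = 0.807.
- Expected losses = 2500 × 0.25 + 1000 × 0.30 = 925.
- Freedman's formula with 2.5:1 allocation: z = √(925 × 2.5) × (1 − 0.807)/(1 + 2.5 × 0.807) = 3.08, so power = Φ(3.08 − 1.96) = 86.9%, which matches 87%.

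The match uses 5-year losses in all 3500 patients, so it presumes full follow-up and complete capture in both groups.

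**Assumptions for the illustration (none is in the article).** No true effect, with 70% survival in both groups, so 2500 × 0.30 = 750 true losses in the AlloSure group and 300 in controls. All 300 control losses are recorded. A share m of AlloSure losses is missed, with m = 5%, 10% or 16.7%. The last value is chosen because it turns 30% into 25%: 0.30 × (1 − 1/6) = 0.25.

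**Formulas.**
- Recorded events: d = 750(1 − m) + 300.
- Missed losses counted as event-free to 5 years: HR = ln(1 − 0.30(1 − m))/ln(0.70).
- Missed losses censored at the moment of loss: HR = 1 − m, because the recorded hazard is (1 − m) times the true hazard.
- Chance of a significant false benefit (Schoenfeld): Φ(|ln HR| × √(d × (2500/3500) × (1000/3500)) − 1.96).

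| Missed share m | d | HR, event-free | False benefit | HR, censored at loss | False benefit |
|---|---|---|---|---|---|
| 0 | 1050 | 1.00 | 2.5% | 1.00 | 2.5% |
| 5% | 1012.5 | 0.94 | 14% | 0.95 | 11% |
| 10% | 975 | 0.88 | 42% | 0.90 | 32% |
| 16.7% | 925 | 0.807 | 84% | 0.833 | 71% |

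One row in full (m = 10%, event-free): recorded risk 0.27; HR = ln(0.73)/ln(0.70) = 0.882; √(975 × 0.2041) × 0.125 = 1.77; Φ(1.77 − 1.96) = 42%. A simulated log-rank test agrees: about 15%, 43% and 85% for the event-free case, and about 11%, 32% and 73% for censoring at loss.

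If patients who leave are censored and leaving is unrelated to graft loss, HR stays at 1.00 and the false-benefit rate at 2.5%.

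**The case against.** The strongest reply is that the registry already covers both groups. Study Design and Outcomes and Measures name a source without excluding another, and AlloSure patients are transplant recipients, so the registry sentence can be read as backing up their survival status too. This stands in part. A reader might infer that the article rules the registry out for AlloSure patients, or that the loss-to-follow-up argument reaches only the controls; the text says neither. But the sentence sits in a power justification, assigns no event source, and fits poorly with a statement that all prospective data come from medical records.

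A second reply is that a condensed article leaves linkage and censoring rules to fuller documents. That is fair as to missing detail. The point here is what the article does state, which differs by group for the primary endpoint.

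Third, capture could be better in the AlloSure group: quarterly draws, care managers, mobile phlebotomy and an app that adds to the record rather than replacing it. This stands. A reader might infer that the bias must favour AlloSure; the article gives neither its size nor its direction.

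A reader might also take the 65% attrition as evidence of heavy under-capture. The article does not explain that figure, and attrition that is censored is not the same as missed events, so it does not support this point.

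**Conclusion.** The concern holds as an unreconciled event source for the primary endpoint that, followed as written, can bias a comparison seeking a 5-point difference. It is not shown that events will be under-captured, nor in which group.

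The figures illustrate sensitivity and are not estimates. They rest on assumed missed shares, complete control capture and no true effect. The claim that missing one AlloSure loss in six (125 of 750) reproduces the whole planned effect is true only if those losses are counted as event-free; censored at the time of loss, the same share gives HR 0.833, not 0.807. Even so, false superiority far exceeds the nominal 2.5% in both cases, unless departures are censored and unrelated to graft loss. The primary endpoint is affected, so this should be settled before the analysis.

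**What to change.** 1. Reconcile Study Design, Outcomes and Measures and the sample-size paragraph, so that each group's source for primary events and for the censoring date is stated once and consistently.
2. For the primary analysis, take graft loss, death and the censoring date from the same registry in both groups, by linking consented AlloSure patients to it.
3. The composite classifies deaths by cause, so apply one cause-of-death rule to both groups, using what the registry records.
4. Use medical-record and app events for a sensitivity analysis and for an agreement check within the AlloSure group. That check would also show how complete the local record is.

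Cost: a data linkage agreement, a possible consent update for patients already enrolled (enrollment began in November 2020), and registry reporting lag at the final analysis. If linkage is already planned in a fuller document, the remaining cost is a sentence of clarification.

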### Outcomes and Measures

The primary endpoint of this study will be superior graft survival measured as the time to allograft loss, defined as the composite of return to dialysis, retransplant, death due to allograft failure, and DWFG (infection, malignancy, and cardiovascular death).

Secondary endpoints include assessment of allograft function and immunological status. Allograft function will be measured as the relative change in eGFR from baseline between the 2 study groups: dd-cfDNA surveillance compared to controls. Immunological status will be defined by detection of de novo DSA formation in patients monitored using dd-cfDNA compared to the matched controls.

All clinical events and investigation results will be captured through the patient electronic medical record or via AlloCare, an optional smartphone-based application that provides a patient-driven platform to manage medications, access results, monitor wellness activities, and streamline communication with their care team. Patients will also be offered mobile phlebotomy when they are unable to visit a local laboratory. The mobile blood draw will be coordinated by CareDx, which will draw all regular tests, urine samples, as well as the AlloSure. Support for testing adherence will be provided by PCMs (CareDx Inc, Brisbane, CA) to assist with scheduling both in-center and mobile draws and provide laboratory visit reminders.

### Testing Schedule

Patients will have quarterly AlloSure dd-cfDNA testing (every 3 months) as part of their posttransplant surveillance for a period of 5 years. DSA, eGFR, routine transplant bloods, and clinical events will be captured using the standard of care regime as per institutional guidelines (Figure 1).

**Figure 1 figure1:**
[figure not shown]
Schedule of testing events. dd-cfDNA: donor-derived cell-free DNA; DSA: donor-specific antibody; eGFR: estimated glomerular filtration rate; EMR: electronic medical record.

In the event of an allograft biopsy (surveillance or for-cause), dd-cfDNA testing is suggested to be drawn prior to the biopsy. For patients with a histological diagnosis of allograft rejection and who are hospitalized, dd-cfDNA are suggested to be measured on alternative days while inpatient and then paired with routine blood tests in the immediate 12 weeks following discharge with the goal to assess the response to treatment.

### Patient Care Managers

PCMs will work directly with participating centers to assist with study protocol adherence and support the integration of the AlloCare phone application. PCMs will coordinate mobile home phlebotomy draws, provide patient education, maintain AlloSure standing order requests in line with the study testing schedule, and provide logistic support to both centers and patients alike.

### Rationale for Testing Schedule

The rationale of the quarterly assessment of dd-cfDNA in the context of renal transplantation is based on key milestones in the posttransplant care of patients and aligns with the routine testing for baseline transplant bloods, urinalysis, and DSA monitoring. Commencing periodic dd-cfDNA surveillance at the 6-month time point posttransplant also complements the transition of care back to community nephrologists for many patients.

Antibody-mediated rejection is widely recognized as the leading cause of transplant failure and accounts for approximately two-thirds of renal allograft losses. Clinical studies over the last 10 years have established that antibodies generated de novo posttransplantation against DSAs are strongly associated and may be an important cause of allograft loss. Detection of a significant level of de novo DSAs should prompt verification of medication compliance and identification of potential sensitization events to minimize the risk of future rejection episodes [19]. Additionally, new data suggest that the elevation of dd-cfDNA precedes de novo DSA formation and correlates with increasing mean fluorescence intensity [12,20]. With the increasing risk of ABMR, assessing dd-cfDNA at these intervals allows practitioners to identify early molecular allograft injury.

Preliminary data are suggestive that elevated dd-cfDNA within the first year posttransplant is associated with significant eGFR decline of 25% in the subsequent year [21]. Quarterly surveillance allows identification of patients that may require increased surveillance and intervention while allowing longitudinal assessment to discern if these trends are appreciated during long-term follow-up.

### Participants

All patients who underwent a kidney transplant within ≥6 months and ≤18 months will be screened to identify patients who are eligible for the study based on inclusion and exclusion criteria. Patients who are eligible to enter the study will be approached for consent during their routine posttransplant clinic visits and will be considered enrolled when they have signed the informed consent form. Selection criteria are shown in Textbox 1.

Study selection criteria.
**Inclusion Criteria**
First draw for purposes of this study ≥6 months and ≤18 months from date of transplantKidney transplant recipient (retransplant and dual kidney permitted)Patient’s health care provider adopts and intends to apply the AlloSure Routine Testing Schedule (quarterly draws)Participant is willing and able to give informed consent for participation in the trialMale or female, aged 12 years or olderIn the investigator’s opinion, patient is able and willing to comply with all trial requirements
**Exclusion Criteria**
Participant who is pregnant, lactating, or planning pregnancy during the trialSignificant hepatic impairment (determined by the principal investigator)Participant with life expectancy of <6 months or inappropriate for diagnostic monitoring through regular blood sampling<6 months and >18 months posttransplantAny other significant disease or disorder which, in the opinion of the investigator, may either put the participants at risk because of participation in the trial or may influence the result of the trial or the participant’s ability to participate in the trialParticipants who have participated in another research trial involving an investigational product in the past 12 weeksRecipients of multiorgan transplant (eg, kidney-pancreas)Recipients of a transplant from a monozygotic (identical) twinRecipients of nonautologous bone marrow transplantPatients with a history of poor compliance or needle phobia

A 2-sided log-rank test with an overall sample size of 3500 kidney transplant patients (of which 2500 will be periodically assessed with AlloSure and 1000 are matched controls receiving standard of care) achieves 87% power at a 5% significance level to detect an allograft survival difference of 5% (ie, 75%, AlloSure assessed; 70%, standard of care) during the 5-year surveillance period. This corresponds to a hazard ratio of 0.807, which is a 19.3% reduction in the risk of allograft loss in the AlloSure-assessed patients in comparison to standard of care. There is no consideration of patients lost to follow-up due to the United Network for Organ Sharing U.S. Scientific Registry of Transplant Recipients database, which tracks transplanted organ survival for all organ transplant recipients; however, this analysis does account for an attrition rate of 65%.

A decline in GFR has been shown to be a valid surrogate for long-term outcome in renal transplantation. A 2-sided *t* test or its nonparametric analog will be used to assess differences in the distribution of 5-year change from baseline in eGFR between AlloSure and standard of care surveillance groups. These tests will have approximately 76% power at a 5% significance level to detect a 25% difference in eGFR decline over the 5-year surveillance period. This assumes, over the 5-year surveillance period, an average of 12 mL/min per 1.73 m^2^ decline in eGFR for standard of care and an average 9 mL/min per 1.73 m^2^ decline in eGFR for AlloSure (both groups having similar standard deviations of 30 mL/min per 1.73 m^2^).

Assuming the proportion of control subjects with formation of de novo DSA antibodies during the 5-year surveillance period is 40%, a 2-sided Z-test with continuity correction and pooled variance with the aforementioned sample size of 3500 achieves 78% power at a 5% significance level to detect a de novo DSA formation difference of 5% (ie, 35%, AlloSure assessed; 40%, standard of care) during the 5-year study surveillance period.

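### The 87% primary power is said to allow for 65% attrition, but it reproduces only with essentially complete 5-year follow-up of all 3500 patients

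*Protocol article*

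**What the plan says.** The sample-size text follows the exclusion criteria in Methods of the protocol article. It begins "A 2-sided log-rank test with an overall sample size of 3500 kidney transplant patients". The split is 2500 in the AlloSure group and 1000 in the matched control group. The design, according to the text, "achieves 87% power at a 5% significance level to detect an allograft survival difference of 5" percentage points: 75% against 70% graft survival over 5 years, a hazard ratio of 0.807.

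Two statements about missing follow-up come next. The first is "There is no consideration of patients lost to follow-up", on the ground that the transplant registry tracks organ survival for all recipients. The second is "however, this analysis does account for an attrition rate of 65" percent. The article does not define attrition, does not say which group it affects, and does not say whether 3500 is counted before or after it.

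The secondary endpoints are powered in the paragraphs that follow. For eGFR: "These tests will have approximately 76% power at a 5% significance level". For de novo DSA: "with the aforementioned sample size of 3500 achieves 78% power at a 5% significance level". Neither paragraph mentions attrition. The Results part of the Abstract gives 3500 (2500 + 1000) as the total sample anticipated.

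**The concern.** The sentence on attrition is a positive claim about what the 87% contains, so it can be tested against the plan's own inputs. An allowance for 65% attrition would have to show up somewhere: as fewer events, as a smaller assumed effect, or as an enrolment target well above 3500. None of these appears in the article.

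At stake is how the primary result will be read. A reader told that 87% power already survives the loss of about two-thirds of patients would take a null result as a well-powered negative. If that attrition happened and the figure had made no allowance for it, such a reading would be unsafe. If the 65% is a slip, the plan carries a false planning assumption.

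**Working it through.** **Inputs (all from the sample-size text).** Groups of 2500 and 1000; 5-year graft survival 75% and 70%; two-sided 5% level (critical value 1.96). eGFR: mean declines of 9 and 12, SD 30. DSA: 35% and 40%, pooled Z-test with continuity correction.

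**Step 1: reproduce the primary power with no attrition.**
- Hazard ratio = ln(0.75)/ln(0.70) = 0.8066, matching 0.807.
- Events = 2500 × 0.25 + 1000 × 0.30 = 625 + 300 = 925.
- Freedman, with allocation ratio φ = 2.5: Z = √(925 × 2.5) × (1 − 0.8066)/(1 + 2.5 × 0.8066) = 3.084. Power = Φ(3.084 − 1.96) = 86.9%, the stated 87%.
- The article does not name its formula. Other approximations with complete follow-up give 84.0% (Schoenfeld) and 86.4% (normal test of the log hazard ratio with variance 1/625 + 1/300). These spreads are ordinary differences between formulas and no fault in the plan.

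**Step 2: reproduce the secondary powers with no attrition.**
- eGFR: 3/(30 × √(1/2500 + 1/1000)) = 2.673; power 76.2% (stated 76%).
- DSA: pooled proportion 1275/3500 = 0.364; null SE 0.0180, alternative SE 0.0182, continuity correction 0.0007; (0.05 − 0.0007 − 1.96 × 0.0180)/0.0182 = 0.77; power 77.9% (stated 78%).

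All three figures therefore use the full 2500 and 1000.

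**Step 3: apply 65% attrition to the AlloSure group, with its events lost.** The controls are historic registry records, so the prospective group is the natural place for attrition.
- *Exponential dropout reaching 65% at 5 years.* Event hazard = −ln(0.75)/5 = 0.0575 per year; dropout hazard = −ln(0.35)/5 = 0.2100 per year. AlloSure events = 2500 × 0.0575/(0.0575 + 0.2100) × (1 − e^(−5 × 0.2675)) ≈ 397. Total = 397 + 300 = 697. Schoenfeld with the 2.5:1 split gives 72.7%. The normal test with variance 1/397 + 1/300 gives 80.2%.
- *Outright loss.* 2500 × 0.35 = 875 AlloSure patients remain; events = 875 × 0.25 + 300 = 519. Freedman (φ = 0.875) gives 67.6%; Schoenfeld gives 68.5%.

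**Step 4: the same outright loss on the secondary endpoints (875 and 1000).**
- eGFR: 3/(30 × √(1/875 + 1/1000)) = 2.160; power 57.9%.
- DSA: (0.05 − 0.0011 − 1.96 × 0.0224)/0.0224 = 0.22; power 58.8%.

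**Step 5: could 65% mean the share retained?** With 35% outright loss in the AlloSure group only (1625 + 1000), primary power is 79–81%. With 35% exponential loss in that group it is at most about 84%. Neither reaches 87%.

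**The case against.** Three defences deserve weight.

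*The 3500 may be the number left after attrition.* Then 87% would be right and would already allow for the 65%. It would need 2500/0.35 ≈ 7143 AlloSure patients enrolled. The full protocol is not shown and might hold such a target, so this cannot be excluded. It is a strained reading, because the Abstract gives 3500 as the whole anticipated sample.

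*Attrition may mean leaving quarterly testing, not losing the outcome.* The sentence sets loss to follow-up aside because of the registry and then introduces attrition as something different. A reader might infer a flat contradiction between its two halves, but the wording does not compel that. The Statistical Analysis section keeps everyone with at least one AlloSure assessment, so graft losses after testing stops might still be counted. This stands in part: the figures for lost events become scenarios. Yet the Study Design section names the registry only as the source of controls. Moreover, patients who stop testing would be expected to pull the observed effect towards the null, and the 5-point difference is stated for AlloSure-assessed patients without any dilution.

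*The 65% is attached only to the log-rank analysis.* This stands. A reader might infer that all three powers are misstated, but the eGFR and DSA paragraphs claim no allowance and are correct for the numbers they name. Carrying attrition over to them is an inference. It is a reasonable one, since the registry argument is made only for organ survival.

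**Conclusion.** As written, the statement that the 87% accounts for 65% attrition is wrong: the figure is that of 2500 + 1000 patients with essentially complete 5-year follow-up. A few percent of loss would hardly change it; 65% would. This assumes that 3500 is the enrolled number.

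If AlloSure patients' events are lost at that rate, primary power is about 73–80% (exponential dropout), some 7 to 14 points below the stated figure, or about 68% (outright loss), some 19 points below. If outcomes are still captured, the shortfall comes through dilution, and its size depends on how much benefit remains after testing stops, which the article does not say.

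A reader might go further and cite 42–45% for the primary endpoint and 35% for each secondary. Those figures need 65% outright loss in both groups (875 + 350), which does not fit controls drawn from historic registry records. Nor should 925 be taken as a target because Study Design says "The study duration will be event driven": it is the count expected under the plan's survival rates, and the article sets no event target.

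**What to change.** Take one of two routes.

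- If 65% is an error, delete or correct it. State that the 87% assumes complete 5-year follow-up of 2500 + 1000 patients, with 925 expected events.
- If 65% is real, define it (stopping testing, withdrawal, or loss of outcome data). Say which group and which endpoints it affects and whether 3500 is counted before or after it. Restate the power of each affected endpoint at that rate. If the registry will supply graft outcomes for patients who stop testing, say so, and say whether the 5-point difference already reflects them.

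Either route is a rewording of the sample-size text. It needs no extra patients; under the second route, if 3500 is the number before attrition, the cost is a less favourable stated power.

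### The 5-year eGFR comparison is fixed as an unadjusted test on change from baseline, which gives up precision that adjusting for the available baseline eGFR could recover, by an amount the protocol does not let us fix

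*Protocol article*

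**What the plan says.** In Methods, Outcomes and Measures, the first secondary endpoint is defined from baseline: "Allograft function will be measured as the relative change in eGFR from baseline between the 2 study groups". The eGFR sample-size paragraph, which follows the selection criteria, names the analysis: a "2-sided *t* test or its nonparametric analog will be used to assess differences in the distribution of 5-year change from baseline in eGFR". It claims "approximately 76% power at a 5% significance level to detect a 25% difference in eGFR decline over the 5-year surveillance period", on the assumption of a "12 mL/min per 1.73 m^2^ decline in eGFR for standard of care" and a "9 mL/min per 1.73 m^2^ decline in eGFR for AlloSure", with "both groups having similar standard deviations of 30 mL/min per 1.73 m^2". The group sizes come from the preceding log-rank paragraph: "2500 will be periodically assessed with AlloSure and 1000 are matched controls receiving standard of care".

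The comparison is not randomised. The Abstract describes the comparator as "1000 propensity-matched historic controls using United Network for Organ Sharing U.S. Scientific Registry of Transplant Recipients data". The matching variables are not listed. The Statistical Analysis section says only that suitable tests will be used; it names no covariate for eGFR.

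**The concern.** The endpoint is a change from baseline, so baseline eGFR is in hand for every patient who enters the comparison. The test named for that endpoint does not use it as a covariate. A change score subtracts the baseline with a coefficient of exactly one. When baseline and follow-up are imperfectly correlated and similarly variable, that is more than the data support: change is then negatively correlated with baseline, and the unadjusted test carries variance that a regression on baseline would remove.

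At stake is the precision of a secondary endpoint whose stated power is already below 80%. The information that could improve it costs nothing extra to collect.

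**Working it through.** **Inputs from the protocol.** Difference in mean decline 12 − 9 = 3 mL/min per 1.73 m²; standard deviation (SD) 30 in both groups, read as the SD of the change; 2500 AlloSure patients and 1000 controls; two-sided 5% level.

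**Reproducing the stated power.**
- SE = 30 × √(1/2500 + 1/1000) = 1.1225
- z = 3 / 1.1225 = 2.673
- Power = Φ(2.673 − 1.960) = 76.2%

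A noncentral t calculation with 3498 degrees of freedom also gives 76.2%. The stated figure is therefore right for the unadjusted t test with all 3500 patients and contains no covariate gain.

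**Adding baseline eGFR as a covariate.** The protocol does not give the correlation rho between baseline and 5-year eGFR, so it is an assumption here, as is an equal SD s at both times. Then:
- Variance of change = 2s²(1 − rho) = 900
- Residual variance after adjustment = s²(1 − rho²) = 900 × (1 + rho)/2
- Residual SD = 30 × √((1 + rho)/2)

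| rho | Residual SD | SE | z | Power | Gain over 76.2% (points) | Implied SD of eGFR at one time, 30/√(2(1 − rho)) |
|---|---|---|---|---|---|---|
| 0.5 | 25.98 | 0.972 | 3.086 | 87.0% | 10.8 | 30.0 |
| 0.6 | 26.83 | 1.004 | 2.988 | 84.8% | 8.6 | 33.5 |
| 0.7 | 27.66 | 1.035 | 2.899 | 82.6% | 6.4 | 38.7 |
| 0.8 | 28.46 | 1.065 | 2.817 | 80.4% | 4.2 | 47.4 |
| 0.9 | 29.24 | 1.094 | 2.742 | 78.3% | 2.1 | 67.1 |

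The last column shows what the equal-SD assumption entails once the SD of change is held at 30.

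**Without the equal-SD assumption.** If c is the correlation between baseline and change, the residual SD is 30 × √(1 − c²). Power is 76.6% at c = −0.1, 80.0% at −0.3 and 87.0% at −0.5. At c = 0 there is no gain.

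**How many patients will have a 5-year eGFR?** The log-rank paragraph expects 75% and 70% allograft survival. If patients with lost grafts have no 5-year eGFR (an assumption; the protocol does not say), 2500 × 0.75 = 1875 and 1000 × 0.70 = 700 remain.
- SE = 30 × √(1/1875 + 1/700) = 1.329; z = 2.258; unadjusted power 61.7%
- Adjusted power: 74.1% at rho 0.5 and 68.8% at rho 0.7

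On that reading, adjustment still adds about 7 to 12 points, but does not bring the comparison to 80%.

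**The case against.** **The article is condensed, and the test appears among power calculations.** A simple test is usual there, and a fuller analysis plan could add covariates. This has some force, and not listing the matching variables is no fault in an article. But the sentence says which test will be used, so it is a stated choice and not a silence.

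**The gain rests on figures outside the document.** This stands. Both rho and equal SDs are assumed, and the largest gain shown belongs to the lowest rho in the table. At rho 0.9 the gain is about 2 points, and it can be nil.

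**A bias claim is tempting but not supported.** A reader might infer that the t test leaves any baseline difference between the groups in the result. It does not. The change score already subtracts baseline, and the variation from chance imbalance is already in the t test's standard error. A reader might also calculate an inflated type I error. At rho 0.5, a 2 mL/min gap would shift mean change by (1 − 0.5) × 2 = 1 mL/min, and z = 1/1.1225 = 0.891 gives about 14% rejection under no effect. That requires the gap to be fixed, systematic and due wholly to regression to the mean, and nothing in the protocol indicates such a gap. If the same gap were instead a stable group difference with parallel decline, the change score would be unbiased and the adjusted model would be shifted by 1 mL/min. With its smaller SE (1/0.972 = 1.029), it would reject about 18% of the time. Which analysis is nearer the truth depends on why baselines differ, and the protocol does not say.

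**The stated 76% might be taken as a safe lower figure.** It is not, since it counts all 3500 patients despite the expected graft losses.

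**Conclusion.** The concern holds as a point about efficiency. The protocol commits a secondary endpoint to an unadjusted test although a potentially useful covariate is available for every analysed patient. With the SD of change at 30, equal SDs and all 3500 patients, the power forgone runs from about 2 points (rho 0.9) to about 11 points (rho 0.5). It is zero if baseline and change are uncorrelated. The 76% is not an arithmetic error: it is correct for the test and numbers assumed.

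The documents do not support a claim that the chosen test is biased, or that adjustment would make this non-randomised comparison unbiased.

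**What to change.** Name as the main eGFR analysis a linear model of 5-year change in eGFR on group, with baseline eGFR as a covariate, and use rank ANCOVA if the data are clearly non-normal. Report the unadjusted change-score comparison beside it. If power is restated, give the assumed baseline to 5-year correlation and the number of patients expected to have a 5-year eGFR. If 76% is kept, label it as the unadjusted figure for all 3500 patients, not as conservative.

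The cost is a line or two of wording, with no new patients or measurements. The model assumes a roughly linear relation with baseline. The larger caution is that, in non-randomised groups, the adjusted and unadjusted results can differ if matching does not balance baseline eGFR well. A material disagreement should then be read as a sign of imbalance and not settled by picking one result.
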